## Methods

### Study Design

This study is a two-arm, facility randomized, open, controlled trial. Of the public-sector health facilities in Ghana that provide ART to PLHIV in conjunction with the National AIDS Control Program (NACP)/Ghana Health Services (GHS), 40 will be randomly and equally allocated to receive either the mHealth intervention or standard of care. Approximately 1600 PLHIV who have been on ART for at least 6 months and who own a mobile phone will be enrolled. Data collection will occur at baseline and 6 and 12 months post-enrollment. A subsample of women and intervention participants from key populations including MSM and FSW, and health care providers and managers at intervention facilities, will be randomly selected to complete qualitative interviews at follow-up.

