### Randomization

Once facilities are identified and agree to participate, they will be randomized within strata (urban/rural and number of ART patients) to the intervention or control group. Facility assignment will be revealed to field staff just prior to study initiation. Group assignment is needed before enrolling individuals and no blinding is possible. Eligible individual participants will receive the intervention or standard of care according to the assignment of the facility where they receive their HIV care and ART medication.

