### Sample Size

We calculated that a sample size of 40 clinics with 40 completed participants per clinic on average for a total of 1600 PLHIV is needed to detect a 15% improvement in adherence at 12 months, with 84% power and a (two-tailed) significance level of 0.05. These calculations assume that, at baseline, 65% of enrolled participants will be defined as having good ART adherence according to national guidelines (>90% adherent in Ghana). We have assumed approximately 20% participant attrition over the life of the study and have increased participant recruitment targets accordingly (N=2000). These calculations assume an intra-class correlation coefficient (ICC) of 0.05 due to the enrollment of participants and randomization by facility. The correlation (stability) in self-reported adherence over time that occurs within both clinics and subjects is assumed to be .50.

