### Study Measures

#### Health Outcomes

Study health outcomes are ART adherence [23,30,31], viral load, retention in care [32,33], and condom use (Table 1). Routine data collection for clinical care related to ART adherence and health outcomes and tracking already occurs in the public sector NACP/GHS health facilities. These data are collected electronically by trained Strategic Information/ Monitoring & Evaluation staff employed by each facility and supervised by the NACP/GHS. This will be augmented with a supplemental data collection form administered to all participants at enrollment and 6 and 12-month follow-ups.

**Table 1 table1:** Overview of measures.

Measures		Indicators	Data source	M0	M6	M12

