### Analysis

#### Primary Analyses

Generalized estimating equations (GEE) will be applied to compare intervention and control arms on the key 6 and 12-month health outcomes. In order to adjust for variance in the outcomes at the facility-level, compound symmetric working correlation matrices will be used in all models. In order to maximize statistical power, all models will control for baseline measures of the outcomes. In addition, all models will include sex, stratification variables, and time on ART, as well as other covariates identified from the literature and to be specified in the final statistical analysis plan. Hypotheses will be tested at the 5% significance level for two-sided comparisons.

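### The retention model is promised a baseline adjustment that cannot exist; each facility's pre-trial retention rate, drawn from records already kept, would supply one cheaply

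*Protocol article*

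**What the plan says.** Under Study Design, of the eligible public facilities, "40 will be randomly and equally allocated to receive either the mHealth intervention or standard of care". Under Randomization, "they will be randomized within strata (urban/rural and number of ART patients) to the intervention or control group". No measure of past facility performance enters the allocation.

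Under Primary Analyses, GEE models compare the arms at 6 and 12 months, and "all models will control for baseline measures of the outcomes". The models also include sex, the stratification variables, time on ART and further covariates drawn from the literature, to be listed in the final analysis plan.

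Table 1 marks adherence and condom use at months 0, 6 and 12, and viral suppression at months 0 and 12. Retention in care is marked at months 6 and 12 only.

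Under Health Outcomes, "Routine data collection for clinical care related to ART adherence and health outcomes and tracking already occurs in the public sector NACP/GHS health facilities", and the article adds that facility staff collect these data electronically. Facility Eligibility and Recruitment requires at least 150 ART patients per facility. Limitations notes that the quality of routine data will need care.

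**The concern.** The commitment to baseline control covers all models, but one of the four health outcomes has no baseline. Retention cannot be measured at enrolment, because being on ART for at least 6 months is an entry condition and every participant has the same value. For this outcome the sentence in Primary Analyses has nothing to act on.

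The consequence is lost precision. With 20 facilities per arm, much of the variance of an arm difference can lie between facilities. If the arms differ by chance in how well their facilities normally retain clients, that difference stays in the retention estimate as noise. The other three outcomes have some protection through participants' own baselines.

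A facility's retention rate before randomisation is a natural substitute. It has a further advantage: assignment is known before individuals are enrolled, so enrolment baselines could in principle be shaped by allocation, while a rate fixed beforehand cannot.

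**Working it through.** **1. The plan's own power figure, and what it already credits.** Sample Size gives "a sample size of 40 clinics with 40 completed participants per clinic on average for a total of 1600 PLHIV" to "detect a 15% improvement in adherence at 12 months, with 84% power and a (two-tailed) significance level of 0.05", with "at baseline, 65% of enrolled participants will be defined as having good ART adherence". It adds "These calculations assume an intra-class correlation coefficient (ICC) of 0.05" and a correlation over time of 0.50 for self-reported adherence within clinics and subjects.

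- Design effect: 1 + (40 − 1) × 0.05 = 2.95. Effective n per arm: 800 / 2.95 = 271.
- Baseline adjustment: variance factor 1 − 0.50² = 0.75. Effective n per arm: 271 / 0.75 = 362.
- 65% v 75% (15% relative is 9.75 points, rounded to 10): power 83.6%, which matches 84%. Without the 0.75 factor, power is 72%.

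The 84% is therefore consistent with an adherence analysis that already takes credit for baseline adjustment. Nothing comparable is available for retention.

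**2. Inputs for retention.** Enrolled per facility: 2000 / 40 = 50 (Sample Size). Prior clients per facility: 150 (the eligibility minimum). Assumed, because the documents do not give them: retention 80%, the retention ICC (0.05 borrowed from adherence, with 0.02 and 0.01 as alternatives) and the year-to-year facility correlation r (0.4, 0.6, 0.8).

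**3. How much lies between facilities.**

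- Between-facility share of variance, L = 50 × ICC / (1 − ICC + 50 × ICC). At ICC 0.05: 2.5 / 3.45 = 0.72. At 0.02: 1 / 1.98 = 0.51. At 0.01: 0.5 / 1.49 = 0.34.
- SD of the chance arm difference in underlying retention = √(ICC × 0.8 × 0.2) × √(2/20). At ICC 0.05: 0.089 × 0.316 = 0.028, or 2.8 points, with a 29% chance of exceeding 3 points. At ICC 0.01: 0.040 × 0.316 = 0.013, or 1.3 points, with about a 2% chance.

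**4. What a prior rate would remove.**

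- Reliability of a rate from 150 clients = 150 × ICC / (1 + 149 × ICC). At ICC 0.05: 7.5 / 8.45 = 0.89. At 0.02: 3 / 3.98 = 0.75. At 0.01: 1.5 / 2.49 = 0.60.
- Share of between-facility variance explained = r² × reliability. Reduction in the variance of the effect = L × r² × reliability.

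| Retention ICC | r = 0.4 | r = 0.6 | r = 0.8 |
|---|---|---|---|
| 0.05 | 10% | 23% | 41% |
| 0.02 | 6% | 14% | 24% |
| 0.01 | 3% | 7% | 13% |

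These figures precede the cost of estimating one more facility-level coefficient, which inflates the variance by about 3%. Multiplying the remaining variance by 1.03 at ICC 0.05 gives 0.897 × 1.03 = 0.92, 0.769 × 1.03 = 0.79 and 0.588 × 1.03 = 0.61. Simulation of 40 facilities at ICC 0.05 gave net reductions of 8%, 21% and 40%. At ICC 0.01 the net reductions are about 0%, 4% and 10%.

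**5. Scale in terms of power (illustration only).** For 80% v 88% retention at ICC 0.05, effective n per arm is 1000 / 3.45 = 290 and the standard error is √((0.16 + 0.1056) / 290) = 0.030. Power is about 75% by the normal approximation (73% by t with 38 degrees of freedom). With variance factors of 0.92, 0.79 and 0.61 it becomes about 78%, 84% and 92% by the normal approximation.

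**The case against.** The strongest reply is that stratified randomisation of 40 facilities, with the strata carried into the model, is standard and valid, and that further covariates are left to an analysis plan that is not shown. Both points are right. The second does not remove the mismatch: the protocol itself fixes baseline control for every model and then gives retention no baseline, and a general reference to covariates from the literature does not supply one.

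The size of the gain is also open to challenge, and this stands. The calculation compares models with and without the prior rate, and neither contains the strata, sex or time on ART. If these already explain part of the facility differences, the gain over the actual plan is smaller. The prior rate would cover all ART clients, whereas the trial enrols phone owners aged 18 to 49 who live nearby, which weakens the correlation. Electronic collection does not guarantee a comparable 12-month rate from every facility. Participants also have some individual care history, since they have at least 6 months on ART and pharmacy refills are recorded at month 0, so the facility rate is not the only possible source of earlier information.

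Stronger readings are tempting but unsupported:

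- A reader might infer that the models adjust only for location and clinic size. They do not: Primary Analyses adds baseline outcomes, sex, time on ART and more.
- A reader might infer a similar loss for adherence. Participants' own baselines carry much of the facility's level, and the stated power is consistent with that credit already being taken.
- A reader might infer that the allocation is deficient. It is not, and no gain from constraining it has been calculated.

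**Conclusion.** The point holds for retention only, as an inexpensive gain in efficiency. The sentence on baseline control cannot be met for retention as Table 1 stands, and a facility's pre-trial retention rate would fill the gap. The plausible benefit runs from almost nothing (ICC 0.01, weak year-to-year correlation) to about a 40% cut in variance (ICC 0.05, correlation 0.8). All of this rests on an assumed 80% retention, an assumed retention ICC and an assumed year-to-year correlation. The retention analysis is valid without the change, and retention is not the outcome on which the sample size rests. This is an improvement worth making, not an error that invalidates anything.

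**What to change.** 1. Before randomisation, extract each facility's ART retention over the previous 12 months, using one definition across all 40 facilities.
2. Pre-specify that rate as a facility-level covariate in the retention model.
3. Reword Primary Analyses to say that adherence, viral suppression and condom use are adjusted for their month-0 values, and retention for the facility's pre-trial rate.
4. Optionally, use the same rate to constrain the allocation within the existing strata. This has to be decided before facilities are randomised, which is still possible because the study stopped before ethics approval and implementation.

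No separate change is needed for adherence.

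The cost is one records extract, one covariate and one cluster-level degree of freedom. If past and current retention turn out to be uncorrelated, about 3% of precision is lost. Poor or inconsistent routine records would shrink the gain.

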### Intervention: LifeLine

The mobile phone intervention, termed LifeLine, was developed and piloted as one component of the Unites States Agency for International Develop (USAID) Ghana project, Strengthening HIV/AIDS Partnerships with Evidence-based Results (SHARPER). SHARPER partners with 25 local non-governmental organizations (NGOs), the Ghana AIDS Commission, and the Ghana Health Service to increase healthy behaviors and access to HIV prevention and care services among MSM and FSW and their intimate partners, and PLHIV and their partners. LifeLine is a one-way text messaging service; participants receive but do not respond to the messages via mobile phone. A local technological partner will provide support for the fully automated LifeLine program, including enrollment of LifeLine participants from mobile phone numbers provided by study staff.

The LifeLine intervention sends daily text message ART reminders at no cost to PLHIV upon enrollment into the program. The messages were developed with input from both PLHIV and members of key populations. Many different messages have been developed and will be rotated approximately every 3 months. Daily messages refer to “medication” rather than drugs or ART, and data from pilot testing showed high acceptability, recall, and sharing of messages. Sample LifeLine messages include:

Taking my medicine every day makes me stay healthy to work and take care of myself and family.”

It is my life and I will make sure that nothing stops me from taking my medicine.”

Good morning! How are you today? Please remember your medication. Stay blessed!”

### Control

In the control condition, participants will receive usual care. This consists of the essential package of services specified by the Ministry of Health Guidelines for Antiretroviral Therapy in Ghana [29]. Services include ART adherence monitoring through self-report and pill counts, in-depth discussion of ART adherence at each treatment visit, regular CD4 testing, management of sexually transmitted infections (STIs), management of opportunistic infections, referrals and linkages within and outside the health system, and regular patient reports through the health information system. For patients who have been on ART for 6 months or more, regular visits are scheduled every 3 to 6 months unless there is an urgent health need, and CD4 testing is conducted twice per year.

### Sample Size

We calculated that a sample size of 40 clinics with 40 completed participants per clinic on average for a total of 1600 PLHIV is needed to detect a 15% improvement in adherence at 12 months, with 84% power and a (two-tailed) significance level of 0.05. These calculations assume that, at baseline, 65% of enrolled participants will be defined as having good ART adherence according to national guidelines (>90% adherent in Ghana). We have assumed approximately 20% participant attrition over the life of the study and have increased participant recruitment targets accordingly (N=2000). These calculations assume an intra-class correlation coefficient (ICC) of 0.05 due to the enrollment of participants and randomization by facility. The correlation (stability) in self-reported adherence over time that occurs within both clinics and subjects is assumed to be .50.

### Study Measures

#### Health Outcomes

Study health outcomes are ART adherence [23,30,31], viral load, retention in care [32,33], and condom use (Table 1). Routine data collection for clinical care related to ART adherence and health outcomes and tracking already occurs in the public sector NACP/GHS health facilities. These data are collected electronically by trained Strategic Information/ Monitoring & Evaluation staff employed by each facility and supervised by the NACP/GHS. This will be augmented with a supplemental data collection form administered to all participants at enrollment and 6 and 12-month follow-ups.

**Table 1 table1:** Overview of measures.

Measures		Indicators	Data source	M0	M6	M12
**Health Outcomes**						
	ART adherence	Self-report in given time period; self-report via visual analog scale; pharmacy refills	Clinical care data; pharmacy records	X	X	X
	Viral suppression	Undetectable plasma HIV viral load (<400 copies/ml)	Laboratory testing	X		X
	Retention in care	Client tracking outcomes: stopped treatment, known to be dead, or lost to follow-up	Clinical care data		X	X
	Condom use	Consistency of use and use at last sex with different partners (main, casual)	Clinical care data	X	X	X
**Implementation Measures**						
	Health behaviors	Self-efficacy for taking ART; perceived social support for adherence; motivation for adherence; perceived quality and access to providers/facilities	Supplemental data collection	X	X	X
	mHealth intervention adoption	Satisfaction with intervention; message receipt and recall; privacy and confidentiality concerns; message relevance and trust; message sharing; actions taken on receiving messages; use of additional mobile phone services	Supplemental data collection; qualitative interviews		X^a^	X^a^
	Fidelity of intervention delivery	Messages sent on-time; messages received	Technology system logs; supplemental data collection		X^a^	X^a^
	Provider perspectives	Benefits and challenges to intervention implementation; intervention impact on PLHIV quality of care; integration with health system	Qualitative interviews			X^b^
**Costing Measures**						
	Costs of routine care	Training; additional staff time; travel for counselors; other	Intervention tracking tool; costing forms	X	X	X
	Costs of intervention	Initial software and hardware/server costs; maintenance for software and server; maintenance for tech support; monthly reporting; SMS costs; message development	Intervention tracking tool; costing forms	X	X	X

^a^Measures administered in intervention facilities only.

^b^Provider interviews will take place approximately nine months after intervention initiation in intervention facilities only.

#### Implementation Measures

This aspect of the study will use a theory-based evaluation approach to assess how and why the mHealth intervention works for PLHIV and key populations on ART [26]. The research will focus on how the mHealth intervention addresses behavioral, social, and cognitive change strategies. Study participants in both intervention and control groups will be asked about their motivation for good health and management of HIV disease in the supplemental data collection form. These health behavior constructs may influence the primary study outcomes, and they may mediate the impact of the mHealth intervention on these outcomes. In addition, to assess reasons for and barriers to mHealth intervention adoption, as well as consistency and timeliness of receipt of text messages, a few questions will be added to the supplemental data collection form for intervention facilities only. Intervention fidelity also will be assessed through review of system logs from the technology provider to check for on-time and same-time of day delivery of text messages to intervention participants.

To explore implementation issues that may be unique for women and/or key populations living with HIV, qualitative in-depth interviews will further assess confidentiality and privacy concerns, message relevance and trust, and other program delivery and adoption issues, in addition to assessing opinions about the motivational aspects of the intervention. Interviews also will include questions about the social support function of mobile phones, probing on how the intervention may increase perceptions of social support from health care providers and PLHIV, as well as how social support may be increased by sharing of messages with family and friends. Finally, interviews will include questions about how participants’ use of the mHealth intervention may have affected their use of mobile phones for other information and services, particularly for women and key populations. A minimum of three interviews per intervention facility will be conducted.

The health care provider qualitative interviews will focus on benefits and challenges to implementing mHealth interventions in health facilities and with clients, as well as to integrating mHealth components into larger health systems in general. One health care provider and one manager will be interviewed in each facility.

#### Costing Measures

Costs will be assessed for implementing the standard of care in NACP/GHS facilities, as well as costs for implementing the LifeLine mHealth intervention. Information from NACP/GHS facility and SHARPER program records will be extracted to account for retrospective and prospective costs, detailed using an Intervention Tracking Tool (ITT) and accompanying prospective costing forms.

### Analysis

#### Primary Analyses

Generalized estimating equations (GEE) will be applied to compare intervention and control arms on the key 6 and 12-month health outcomes. In order to adjust for variance in the outcomes at the facility-level, compound symmetric working correlation matrices will be used in all models. In order to maximize statistical power, all models will control for baseline measures of the outcomes. In addition, all models will include sex, stratification variables, and time on ART, as well as other covariates identified from the literature and to be specified in the final statistical analysis plan. Hypotheses will be tested at the 5% significance level for two-sided comparisons.

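### Four health outcomes at up to two follow-up times are tested at 5% with no single primary outcome, and the adherence indicator behind the sample size is not named

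*Protocol article*

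**What the plan says.** Under Health Outcomes, the protocol article lists four outcomes without rank: "Study health outcomes are ART adherence [23,30,31], viral load, retention in care [32,33], and condom use". Table 1 gives adherence three indicators: "Self-report in given time period; self-report via visual analog scale; pharmacy refills". It schedules adherence, retention and condom use at both follow-ups and viral suppression at 12 months only.

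The Primary Analyses section uses GEE to "compare intervention and control arms on the key 6 and 12-month health outcomes" and fixes the test level: "Hypotheses will be tested at the 5% significance level for two-sided comparisons". The Implementation Measures section refers to the primary outcomes in the plural.

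Two other sections each lean on a single outcome, but not the same one. Sample Size is built on good adherence at 12 months and assumes: "The correlation (stability) in self-reported adherence over time that occurs within both clinics and subjects is assumed to be .50". Cost Effectiveness Analysis uses viral suppression at 12 months. Neither section calls its outcome primary.

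Study Design describes the trial as open, and Randomization says that blinding is not possible. Limitations concedes that self-reported adherence is weak and promises to set it beside pharmacy, clinician and laboratory data.

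**The concern.** If every key outcome at each follow-up is primary and tested at 5%, the trial can be declared positive on any of them, and the overall false-positive risk is well above 5%. The section that fixes the sample size suggests one deciding outcome, but the section that fixes the tests does not adopt it.

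Even within adherence the deciding measure is open: two self-report indicators and one refill indicator could each be the outcome that was sized. The correlation assumption suggests self-report. Intervention participants receive daily prompts to take their medication and then report whether they did, knowing their arm. Self-report could therefore improve while refills and viral load do not. The article promises to look at all of these measures but sets no rule for reading such a disagreement.

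**Working it through.** **1. The plan's own power figure.** Inputs from Sample Size and Study Design: 40 clinics, equal allocation, 40 completers per clinic (800 per arm), ICC 0.05, correlation 0.50, 65% with good adherence, two-sided 0.05.

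- Design effect: 1 + (40 − 1) × 0.05 = 2.95.
- Baseline-adjustment factor: 1 − 0.50² = 0.75.
- Effective n per arm: 800 / 2.95 / 0.75 = 361.6.
- 65% versus 75% (about a 15% relative gain): standard error √[(0.65×0.35 + 0.75×0.25)/361.6] = 0.0339. Then 0.10/0.0339 − 1.96 ≈ 0.99, so power is 83.9% (83.7% with the pooled form).

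This matches the stated 84%. Exactly 1.15 × 65% = 74.75% gives 81.7% (pooled). An absolute 15-point gain gives 97.6% or more and does not match. The calculation spends the full 5% on one outcome at one time.

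**2. Number of tests.** From the follow-up columns of Table 1, with one test per outcome per time:

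- adherence at 6 and 12 months: 2
- viral suppression at 12 months: 1
- retention at 6 and 12 months: 2
- condom use at 6 and 12 months: 2

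Total: 7. The Abstract gives both times for all four outcomes, including viral load, and should be reconciled with Table 1.

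**3. Chance of at least one false positive when there is no effect on any outcome.** For k independent tests at 5% it is 1 − 0.95^k; for k = 7, 1 − 0.95⁷ = 30.2%. For correlated tests it comes from simulating equally correlated normal test statistics (400,000 draws). The correlations are assumptions, since the article gives none between outcomes.

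| Tests | Independent | Correlation 0.5 | Correlation 0.9 |
|---|---|---|---|
| 4 (one per outcome) | 18.5% | 15.7% | 9.4% |
| 7 (outcome by time) | 30.2% | 22.8% | 11.4% |

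**4. Two ways to bring it back to 5%.**

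- Name 12-month adherence as the only primary outcome. Error is 5% and power stays at about 84%, because this is what was sized.
- Keep all 7 as co-primary with a Bonferroni correction. The level per test is 0.05/7 = 0.0071, and power for adherence (65% versus 75%) falls from 83.7% to 59.7%.

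**The case against.** The strongest reply is that this is a condensed article whose analysis plan is not shown, and multiplicity methods are often left to that plan. That stands for the choice of method. It does not cover which outcome decides the trial, which is a protocol-level statement. Nor does the article leave the matter open: it places all the key outcomes under Primary Analyses and sets the test level there. It defers only further covariates to the analysis plan.

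It can also be said that 12-month adherence is the implicit primary outcome because the trial is sized on it. That is a fair inference and is the basis of the fix, but the article never says so, and three indicators could fill the role. A single GEE model could also cover both follow-ups with one test per outcome. Even then, four tests give 9.4% to 18.5%.

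A reader might infer three stronger points, which the documents do not support:

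- **Every Table 1 indicator is a separate confirmatory test.** Counting each indicator, with condom use split by partner type, gives 3×2 + 1 + 2 + 2×2×2 = 17 tests and 1 − 0.95¹⁷ = 58%. The article nowhere says that each indicator is tested separately, and Limitations presents the adherence sources as complementary.
- **Over-reporting has a known size.** A 5-point difference between arms in over-reporting would raise the false-positive rate for adherence to about 29%, and a 2-point difference to about 9%. Both differences are assumptions with no basis in the article. Control participants also discuss adherence in depth at each treatment visit, so pressure to over-report exists in both arms and only the unknown difference matters.
- **Pharmacy refill must be the primary measure.** Limitations itself names medication supply as an outside factor that may confound results, and refill records would be exposed to it. A change of measure would also reopen the sample size.

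**Conclusion.** The point holds in this form: the protocol treats four health outcomes at up to two follow-up times as primary at an uncorrected 5%, sizes the trial on only one of them, and does not say which adherence indicator that one is. With the minimum of 7 tests, the chance of at least one false positive is 30% if they are independent, about 23% at correlation 0.5 and 11% at 0.9. It exceeds 5% across the range shown. These figures assume one test per outcome per scheduled follow-up, no true effect on any outcome, and the stated correlations.

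That the sized measure is self-report is an inference from the correlation assumption, not a statement in the article. The lack of blinding makes an interpretation rule worth having, but the documents do not allow the bias to be quantified.

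**What to change.** In Health Outcomes and Primary Analyses:

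- Name one primary outcome: the proportion with >90% adherence at 12 months, as sized, on one stated indicator.
- Make 12-month viral suppression the first secondary outcome, tested at 5% only if the primary result is significant.
- Report the other adherence indicators, all 6-month results, retention and condom use as secondary or supportive estimates with confidence intervals.
- If the chosen indicator is self-report, state that a gain will be interpreted alongside the refill and viral-load results, and that a gain they do not support will not be claimed as an effect on adherence.
- Align the plural reference to primary outcomes in Implementation Measures, and the viral-load time points in the Abstract, with these statements.

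The cost is wording. Refill and viral-load data are already in Table 1, the sample size does not change, and the study was stopped before ethics review and implementation, so the text can still be revised. The downside is that the other outcomes lose confirmatory status.

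Choosing refill or viral suppression as the primary outcome is an option. The 65% rate, the 0.50 correlation and the ICC of 0.05 would then need re-checking for that measure, and the article gives no suppression rate from which to compute power.
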